**Table: Follow-up**

|  | **Selection inclusion** | **V0** | **V1**  **3** weeks | **V2**  **6** weeks | **V3**  **3 months** | **V4**  **6 months** |
| --- | --- | --- | --- | --- | --- | --- |
| Inclusion  Zelen randomization  Consent | X  X  X |  |  |  |  |  |
|  |  |  |  |  |  |  |
|  |  |  |  |  |  |  |
| Sociodemographic data | X |  |  |  |  |  |
| History of OA | X |  |  |  |  |  |
| Clinical examination | X |  |  |  |  |  |
| X-ray | X |  |  |  |  |  |
| Ultrasonography | X |  |  |  |  |  |
| Treatment | X | X | X | X | X | X |
| VAS pain | X | X | X | X | X | X |
| Clinical follow-up |  | X | X | X | X | X |
| WOMAC |  | X | X | X | X | X |
| Quality of life |  | X | X | X | X | X |
| Posturography |  | X | X | X | X | X |
| 6-minute walking test |  | X | X | X | X | X |
| Care consumption |  | X | X | X | X | X |
| Adverse reactions |  |  | X | X | X | X |
| Satisfaction, heiQ |  |  | X | X | X | X |

**4.3. DESCRIPTION OF THE MEASURES TAKEN TO REDUCE AND AVOID BIAS**

Randomization

Most literature reviews emphasize the importance of blinding of the assessor [44,45,46,47] and randomization [48,49,50] in a therapeutic trial. In the context of thermal care, it is impossible to blind the patient, which can lead to a bias of therapeutic preference [51]. The Zelen randomization method (randomization method before consent is obtained) must allow for reducing this bias. This method has been used successfully in the past [52,53]. For some, it has the additional advantage of reducing the number of refusals to enter the study [54]. A review published in 2006 shows that among 58 studies, this method was more frequently used to limit bias than to increase recruitment [55]. This method does not contradict the rules of ethics and is widely used in many studies.

Because patients cannot be completely blinded, randomization will be according to the Zelen method [51]. During the inclusion visit, patients will be informed that the purpose of the research is to study the effectiveness of the care provided during spa therapy. The content of spa therapy will not be explained in detail right away and randomization will occur before consent is obtained. In the event of refusal after allocation of the intervention group (e.g., the patient not wishing to undergo care for 6 weeks), the patient will be assigned to the other group. An information letter and a consent specific to each group will be proposed.

Randomization will be performed centrally and independently by use of a computer program at the Centre for Clinical Epidemiology (CIC EC). The randomization group will be available during the selection visit.

(b) Blinding methods.

The assessor will be blinded to the treatment group at 3 and 6 months.

**4.4. EXPERIMENTAL DRUGS / MEDICAL TREATMENTS UNDER STUDY**

NA

**4.5. EXPECTED DURATION OF PARTICIPATION OF PERSONS AND DESCRIPTION OF THE CHRONOLOGY AND DURATION OF ALL TRIAL PERIODS, INCLUDING FOLLOW-UP, IF NECESSARY.**

Inclusion visit

The investigating physician verifies that the patient meets the inclusion criteria defined in advance, during a consultation carried out in the rheumatology department of Nancy University Hospital, Vandoeuvre les Nancy.

This physician will ensure that the patient has a knee X-ray performed according to current recommendations to verify the eligibility criteria. If necessary, a digitized radiograph will be taken in the rheumatology department.

After randomization, the investigating physician gives the eligible patient the information form that corresponds to the type of cure selected and obtains his/her consent to enter the study.

A plan is given to the patient.

Follow-up visits

Subsequent visits will all take place at the Nancy Thermal site in the spa center. They will involve the thermal physician and/or the assessor who will collect the data necessary for the study (V0, V1, V2, V3 and V4) (see monitoring table). The thermal physician also ensures the medical follow-up of the treatment and collects adverse reactions.

Occupancy, group planning:

This study will be conducted from mid-March to mid-December 2012. The flow of patients has been planned for both types of treatment: "classic spa therapy", “active spa therapy". A subgroup will consist of a maximum of 8 patients. Over 6 weeks and for each type of spa therapy, 4 subgroups can be included, i.e., 32 patients randomized in each group (64 patients). The study will focus on 5 cycles of 6 weeks for a total time of 30 weeks.

In the morning, the premises, care and carers will be dedicated to the "classic spa therapy" group, i.e., a daily occupation over 3 consecutive weeks for 2 subgroups of patients or over 6 weeks for 4 subgroups of patients.

In the afternoon, the premises, care and carers will be dedicated to the group “active spa therapy" for 3 weeks of usual spa therapy, then 3 weeks of rehabilitation/education by alternating sub-groups on alternate days, i.e., a daily occupation over 6 weeks for 4 subgroups.

This organization will allow for the same premises for both groups ("classic spa therapy" and “active spa therapy") while avoiding that they are in close contact, comparing their care while avoiding shifting the groups over time.

Coordination

Coordination, logistics management, quality control, data management, and statistical data processing will be carried out by the CIC EC in Nancy.

Expected inclusion period: from January 2012 to the end of October 2012, i.e., 10 months

Duration of participation (including follow-up period): for one patient, 6 months from the beginning of the spa therapy

Total duration (including data analysis time): December 2011 to mid-October 2013 or 2 years

|  | **Selection inclusion** | **V0** | **V1**  **3** weeks | **V2**  **6** weeks | **V3**  **3 months** | **V4**  **6 months** |
| --- | --- | --- | --- | --- | --- | --- |
| Inclusion  Zelen randomization  Consent | X  X  X |  |  |  |  |  |
|  |  |  |  |  |  |  |
|  |  |  |  |  |  |  |
| Sociodemographic data | X |  |  |  |  |  |
| History of OA | X |  |  |  |  |  |
| Clinical examination | X |  |  |  |  |  |
| X-ray | X |  |  |  |  |  |
| Ultrasonography | X |  |  |  |  |  |
| Treatment | X | X | X | X | X | X |
| VAS pain | X | X | X | X | X | X |
| Clinical follow-up |  | X | X | X | X | X |
| WOMAC |  | X | X | X | X | X |
| Quality of life |  | X | X | X | X | X |
| Posturography |  | X | X | X | X | X |
| 6-minute walking test |  | X | X | X | X | X |
| Care consumption |  | X | X | X | X | X |
| Adverse reactions |  |  | X | X | X | X |
| Satisfaction, heiQ |  |  | X | X | X | X |

**4.6. PROCEDURES FOR ACCOUNTING FOR EXPERIMENTAL MEDICINAL PRODUCTS**

NA

**4.7. PROVISIONS IMPLEMENTED TO MAINTAIN BLINDING AND** PROCEDURES **TO REMOVE THE BLINDING, IF NECESSARY.**

NA

**4.8. IDENTIFICATION OF ALL DATA TO BE COLLECTED DIRECTLY IN THE OBSERVATION WORKBOOKS, WHICH WILL BE CONSIDERED AS SOURCE DATA.**

**Assessment tools**

Data collection will be carried out by the investigating physician at the time of inclusion then by the thermal physician and the assessor at other times.

Sociodemographic and clinical examination data:

The following demographic and clinical characteristics will be collected: age, sex, socioeconomic data, risk factors associated with knee OA, comorbidity index, drug, clinical examination (weight, height, static lower -limb disorders, uneven length of the lower limbs, joint effusion, meniscal test, mobility of the knee joint, examination of the hip and spine, 6-minute walking test). The 6-minute walking test is easy to implement and allows for assessing the direct impact of OA on walking [56], judging the effectiveness of a valgisation orthosis in knee OA [57] and for predicting the effectiveness of total hip arthroplasty [58].

Patient-reported outcome measures

WOMAC index

It will be used as the basis for calculating the main outcome criterion. It was developed by Bellamy in 1988 [60] and is now more widely used than the Lequesne index and has a good sensitivity to change [61].

VAS-Pain

Pain measurement will be measured on a VAS according to Huskinsson [62]. We will use one of the recommended methodologies by the French High Authority for Health.

Quality of life (QoL)

The SF-36 is a generic quality of life instrument that has been widely used since 1992 [63]. It was recently used to evaluate the effectiveness of spa treatment during knee OA [64]. OAKHQOL is a QoL instrument specific for knee and/or hip OA [3]. This tool is used to evaluate the effectiveness of treatment during knee OA (viscosupplementation, total joint replacement surgery)[65, 66].

X-rays

Each patient included should have knee X-rays < 6 months old with a femoro-tibial incidence in Schuss position and a femoral-patellar incidence of 60°. A radiographic evaluation according to the Kellgren and Lawrence classification will be performed by the investigating physician during the inclusion visit [5].

Ultrasonography

This examination is carried out by the investigating physician. It allows for classifying knee OA in congestive or non-congestive forms at inclusion. This non-radiant and non-traumatic exam will help to appreciate the importance of joint effusion and synovitis and to objectify the presence of a popliteal cyst by using a score validated for the first time in this type of population [6]. Joint effusion and synovitis will be evaluated on 3 regions of interest: median, medial and lateral quadricipital ramps. The vascular activity of synovitis will be explored in power Doppler mode.

The presence of a popliteal cyst will be sought in the ventral decubitus.

The effusion varies from 0 to 9 and will be considered positive at ≥ 1. The synovitis score ranges from 0 to 15 and will be considered positive at ≥ 1.

The presence of a popliteal cyst will be rated binary: present or absent [6].

Posturography

The posturography examination will be the responsibility of [name] and his team. The examination will be conducted by using a movable platform in a room with sound insulation to avoid interference. The posturography examination is performed without and then with the use of glasses of virtual reality that will distort vision (eyes open/closed/vision distorted) in static and then dynamic situations (foam or swashplate).

At least 6 data points will be acquired. The examination will assess the components proprioceptive, visual and vestibular that come into play in the individual's postural balance [4]. Proprioceptive control appears to fail during knee OA [11], but this study will make it possible to measure the impact of the classical and active spa therapy by measuring the change in length travelled and/or the area covered by the foot pressure centre after the suppression or disruption of sensory inputs and/or somesthesics during treatment and follow-up[ 4]. A recent review showed that active rehabilitation improves control proprioceptive [59].

**The main and secondary evaluation criteria**

Main criterion

# The MCII in OA was determined by Tubach et al. [2]. The MCII is a threshold for improvement which is particularly suitable for therapeutic trials and takes into account that the MCID may be different for an improvement or a worsening. A patient is considered improved if the WOMAC index function subscale score is improved by at least 9.1 from the initial value and/or if the current pain measured on a VAS is improved by at least 19.9 mm. These values correspond to the smallest clinically relevant change for these two outcome criteria [2]. Improvements below this value will be considered treatment failures. Patients with improvement but who still need surgery during the period of the study will also be considered failures. The effect of two types of spa therapy ("standard spa therapy" and "active spa therapy") for symptomatic knee OA will be assessed by proportion of patients who have achieved a composite criterion combining the MCII for pain and/or functional abilities and the absence of knee surgery of the target knee at 6 months.

Secondary criteria

- Percentage of patients reaching MCII (pain, function and composite score) at the end of the treatment and at 3 months
- Percentage of patients reaching the PASS (pain and function) at 3 and 6 months [14]. The PASS is the value beyond which the patient considers himself/herself to be well. It is defined as for the MCII by the 75th percentile of the score among the patients whose assessment of the acceptable symptom state was “good” on a Likert scale with 5 answer modalities. The PASS has been determined for WOMAC function at 31 mm and for VAS for pain at 32 mm [14].
- Evolution of quality of life scores (OAKHQOL, SF-36) at 3 and 6 months
- Evolution of VAS-fatigue, VAS-pain at 3 and 6 months
- Evolution of WOMAC scores (function) at 3 and 6 months
- Patient satisfaction (overall VAS or heiQ module 9) at 3 and 6 months
- Evolution of drug and care consumption, use of surgery
- 6-minute walking test [43]
- Evolution of posturography parameters: modification of the length travelled and/or the area covered by the pressure centre of the feet after the removal or disruption of sensory inputs, somesthesics of balance in distorted visual situations, and static and dynamic positions [4]
- Adverse reactions

**4.9. COLLECTION OF BIOLOGICAL SAMPLES**

NA

**5. INCLUSION AND EXCLUSION OF PEOPLE FROM RESEARCH:**

5.1. INCLUSION CRITERIA

The patients with knee OA:

- Meeting the criteria for knee OA of the ACR (*)
- Uni- or bilateral OA
- Symptomatic: VAS pain > 3 on a scale of 0 to 10
- Radiological femoro-tibial knee OA³ stage 2 of the Kellgren and Lawrence classification
- With consent
- Preliminary medical examination

* The diagnostic criteria used are those of the ACR [Altman 1986]:

- Knee pain and at least 1 of the following three criteria:
  - Age > 50 years old
  - Morning stiffness < 30 min
  - Crepitus on active motion
- The presence of osteophytes on knee X-rays

(sensitivity 94%, specificity 87%)

5.2. NON-INCLUSION CRITERIA

- Isolated patellofemoral OA
- Indication for total joint replacement surgery within 1 year
- Contraindication to spa therapy (immune deficiency, moderate to severe heart failure, cancer, infection, skin wound etc.) or predictable intolerance to spa therapy (intolerance to heat, baths, hot tubs, swimming pool etc.)
- Other disease of the musculoskeletal system (inflammatory arthritis, disabling lumbar radiculopathy, motor deficit of the lower limbs)
- Severe comorbidities
- Severe depressive syndrome, psychosis
- Previous knee treatments:
  - Massages, physiotherapy, acupuncture of M 1 month
  - NSAID change within the last 5 days
  - Change of analgesics within the last 24 hr
  - Change of symptomatic slow-acting drugs in OA of < 3 months
  - Intra-articular injection of the target joint of < 1 month for corticoids and < 3 months for viscosupplementation
  - Physiotherapy or rehabilitation of < 1 month.
  - Spa therapy during the previous year

**5.3. PROCEDURE FOR EARLY TERMINATION OF THE RESEARCH OR EXCLUSION (DISCONTINUATION OF TREATMENT + DISCONTINUATION OF FOLLOW-UP)**

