**5.3.1. CRITERIA AND PROCEDURES FOR STOPPING PROCESSING / AND EXCLUSION**

- FINAL STOP: In case of a serious adverse reaction

- No prohibition to participate in another protocol

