**5.3.2. DATA COLLECTION AND MONITORING PROCEDURES**

The follow-up visits will all take place at the Nancy Thermal site in the spa center. They will be carried out by the thermal physician and/or the assessor who will collect the data necessary for the study (V0, V1, V2, V3 and V4) (see monitoring table). The thermal physician also ensures the follow-up medical treatment and collects adverse reactions.

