**5.3.4 PROCEDURES FOR MONITORING PEOPLE**

NA

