# The MCII in OA was determined by Tubach et al. [2]. The MCII is a threshold for improvement that is particularly suitable for therapeutic trials and takes into account that the MCID may be different for an improvement or a worsening. A patient is considered improved if the WOMAC index function subscale score is improved by at least 9.1 from the initial value and/or if the current pain measured on a VAS is improved by at least 19.9 mm. These values correspond to the smallest clinically relevant change for these two outcome criteria [2]. Improvements below this value will be considered treatment failures. Patients with improvement but would still need to have surgery during the study period will also be considered failures. The effect of the two types of spa therapy ("standard spa therapy" and "active spa therapy") for symptomatic knee OA will be assessed by proportion of patients who achieve a composite criterion combining the MCII for pain and/or functional abilities and the absence of knee surgery of the target knee at 6 months.

Secondary criteria

- Percentage of patients reaching the MCII (pain, function and composite score) at the end of the treatment and at 3 months
- Percentage of patients reaching the PASS (pain and function) at 3 and 6 months [14]. The PASS is the value beyond which the patient considers himself/herself to be well. It is defined as for the MCII by the 75th percentile of the score among patients whose assessment of the acceptable symptom state was “good” on a Likert scale with 5 answer modalities. The PASS for WOMAC function is 31 mm and for VAS for pain is 32 mm [14].
- Evolution of quality of life scores (Osteoarthritis Knee and hip Quality of life [OAKHQOL], SF-36) at 3 and 6 months
- Evolution of VAS-fatigue, VAS-pain at 3 and 6 months
- Evolution of WOMAC scores (function) at 3 and 6 months
- Patient satisfaction (overall VAS or heiQ module 9) at 3 and 6 months
- Evolution of drug and care consumption, use of surgery
- 6-minute walking test [43]
- Evolution of posturography parameters: modification of the length travelled and/or the area covered by the pressure centre of the feet after removal or disruption of sensory inputs, somesthesics of balance in distorted visual situations and static and dynamic positions [4]
- Adverse reactions

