**8.4. MODALITIES AND DURATION OF FOLLOW-UP OF PERSONS FOLLOWING THE OCCURRENCE OF UNDESIRABLE EVENTS**

When a serious adverse event persists, including after the end of the study, the investigator will follow the patient until the event is considered resolved and will forward the follow-up data to the appropriate body.

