**Comparison of groups**

The trial being a non-inferiority trial, the main analysis will be per protocol to be conservative by increasing the contrast between the groups.

Main objective

The active spa therapy will not be considered inferior to the standard spa therapy if the lower bound of the confidence interval at 90% of the difference between the 2 groups (active spa therapy minus standard spa therapy) for the main outcome criterion (percentage of respondents according to the composite criterion) is not less than 15%[1]. After verification of the randomization that could be unbalanced owing to the Zelen randomization mode, the final analysis will be adjusted if necessary on the variables that differ between the 2 groups.

Secondary objectives

- The same analyses will be repeated for the MCII composite criterion, pain and function at 3 months and for PASS criteria.

- To determine the predictive factors of spa therapy response, a bivariate analysis will be performed using chi-square tests (or Fisher exact tests depending on the number) for discrete variables, and Student t-tests, ANOVA or Wilcoxon tests for quantitative variables. The parameters significant on bivariate analyses (at the conservative threshold of p=0.1) will then be introduced into a stepwise multiple logistic regression.

A value of p<0.05 will be considered statistically significant.

The statistical analysis will be carried out by the Centre for Clinical Epidemiology by using SAS v9.2 (SAS Inc., Cary, NC).

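### Section 5.3 ties stopping treatment to stopping follow-up, so the 6-month outcome of patients stopped for a serious reaction is not secured

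*Protocol*

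**What the plan says.** The heading of Section 5.3 covers early termination or exclusion and explains the latter as "EXCLUSION (DISCONTINUATION OF TREATMENT + DISCONTINUATION OF FOLLOW-UP". Four subsections bear on what follows:

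- Section 5.3.1 names one event and one status: "FINAL STOP: In case of a serious adverse reaction". It adds that the patient may join another protocol. It has no category for a patient who is off treatment but still followed.
- Section 5.3.2 states that "The follow-up visits will all take place at the Nancy Thermal site in the spa center", and lists V0 to V4. It largely repeats the visit text of Section 4.5 and does not mention patients who have stopped.
- Section 5.3.4, "PROCEDURES FOR MONITORING PEOPLE", is marked not applicable.
- Section 8.4 says that, when a serious adverse event persists, "the investigator will follow the patient until the event is considered resolved". This is safety follow-up; pain and function scores are not mentioned.

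The composite in Section 7.1 has two routes to failure. On insufficient change: "Improvements below this value will be considered treatment failures". On surgery: "Patients with improvement but would still need to have surgery during the study period will also be considered failures". Stopping the cure for harm is not among them. In Section 9, "the main analysis will be per protocol to be conservative by increasing the contrast between the groups"; no analysis of all randomised patients is stated.

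**The concern.** Followed literally, the heading and Section 5.3.1 take a patient who has a serious reaction during the cure out of both treatment and follow-up. That patient then has no 6-month pain or function value, and no rule in the composite makes the stop itself a failure. Patients who stop because of harm are unlikely to be a random sample with respect to response, so their absence can shift the observed responder proportions.

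Analysis sets and the handling of missing values can be left to an analysis plan. Whether the outcome is collected cannot: what the protocol ceases to record can later only be assumed. At stake are the completeness of the primary outcome in a non-inferiority comparison and the quality of any supporting analysis in all randomised patients.

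**Working it through.** **Inputs from the protocol (Section 9).** Standard-arm responders 50%; margin 15 percentage points, read here as a lower limit of −15 points for active minus standard; 90% confidence interval, hence one-sided 5%; power 80%; 135 per group; 5% loss; 284 in total, that is 142 per arm.

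**Inputs assumed.** The protocol gives no stop rate for either arm, so a range is used. Every stopped patient is taken as a non-responder who leaves the denominator. The truth is placed exactly at the margin, 50% against 35%.

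**Step 1: the plan's own figure.** n = [0.5×0.5 + 0.5×0.5] × (1.645 + 0.842)² / 0.15² = 137.4, so 138 per group, within 3% of the stated 135. Power at 135 per group is 79.4%. For the total, 2 × 135 / 0.95 = 284.2, which agrees with 284. The test is therefore understood as the protocol intends.

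**Step 2: effect of losing stoppers.** With share s stopped, the observed rate is p/(1 − s) on 142(1 − s) patients. The chance of claiming non-inferiority is Φ[(p_active − p_standard + 0.15)/SE − 1.645], with unpooled SE.

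Example, 2% stopped in the active arm only: 0.35/0.98 = 0.3571 on 139.2 patients; SE = √(0.25/142 + 0.3571×0.6429/139.2) = 0.0584; 0.0071/0.0584 − 1.645 = −1.523; probability 6.4%.

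| Stopped, standard | Stopped, active | Observed difference (points) | False non-inferiority |
|---|---|---|---|
| 0% | 0% | −15.0 | 5.0% |
| 0% | 1% | −14.6 | 5.7% |
| 0% | 2% | −14.3 | 6.4% |
| 0% | 5% | −13.2 | 9.1% |
| 1% | 1% | −15.2 | 4.7% |
| 2% | 2% | −15.3 | 4.5% |
| 5% | 5% | −15.8 | 3.8% |
| 1% | 0% | −15.5 | 4.2% |
| 2% | 0% | −16.0 | 3.4% |
| 5% | 0% | −17.6 | 1.8% |

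**Step 3: break-even.** The error exceeds 5% only if 0.35·s_active/(1 − s_active) is greater than 0.50·s_standard/(1 − s_standard). With 2% stopped in the standard arm, the active arm must lose more than about 2.8%; with 5%, more than about 7.0%.

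**Step 4: which rows are plausible.** The only listed trigger is a serious reaction, and Section 8.1 calls serious problems exceptional. The 1% and 2% rows (0.01 × 142 = 1.4 and 0.02 × 142 = 2.8 patients per arm) fit that description better than the 5% rows.

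**Step 5: if the outcome is collected.** When stopped patients are followed and counted by their actual response, the error at the margin stays at 5.0% and the required number does not change.

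**The case against.** The strongest reply is that the reading rests on a heading. The parenthesis may only list what the section covers, while Section 5.3.2 sets out visits to 6 months with no exemption for patients who stop. That makes the text ambiguous but does not settle it: Section 5.3.2 does not refer to stopped patients, and if it includes them it contradicts its own heading. The passages need reconciling either way.

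A second reply is that a patient without a 6-month value has not shown response and could be counted as a failure under an analysis plan. That is fair, and it means an analysis of all randomised patients would not be impossible. It would, however, rest on an assumption where a short questionnaire could supply the answer.

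A reader might go further and infer that Section 5.3 makes a false non-inferiority claim more likely. The documents do not support that. The active course is longer and includes strengthening, which could produce more stops. But the standard arm has 18 thermal sessions against 9 (Section 6.1), the serious risks named in Section 8.1 (cardiac problems and warm-water infection) are thermal ones, and Section 2 reports that patients sometimes find the standard regimen intense and tiring. The excess could lie in either arm, and with equal stops the effect reverses.

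Nor do the documents say that patients stopping for non-serious effects or by choice lose follow-up; on them Section 5.3 is silent. Finally, the per-protocol primary analysis could omit stopped patients even if they were fully followed, so the loss cannot be blamed on Section 5.3 alone.

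**Conclusion.** The point holds as a gap in outcome collection, with no fixed direction of bias. Sections 5.3, 5.3.1, 5.3.2 and 5.3.4 do not together secure the 6-month outcome of a patient stopped for a serious reaction, and the composite does not say how such a stop counts.

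If stoppers are non-responders and the truth is at the margin, false non-inferiority rises to about 5.7% to 6.4% when 1% to 2% stop in the active arm only. With the same 1% to 2% in both arms it falls to 4.7% to 4.5%, and with stops in the standard arm only to 4.2% to 3.4%. The stop rates are assumptions, and the real effect is probably small. This is an inexpensive improvement worth making; it does not by itself put the trial's conclusion in doubt.

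**What to change.** - Reconcile Sections 5.3, 5.3.2 and 5.3.4 by defining stop of treatment and stop of follow-up as separate events, and drop the second from the heading's explanation of exclusion.
- State in Section 5.3.4, in place of the not-applicable entry, that every randomised patient stays in V1 to V4 after stopping the cure, unless consent to follow-up is withdrawn. Because randomisation precedes consent here, this can apply only to those who gave consent.
- For patients who will not return to the spa centre, collect VAS pain, WOMAC function and target-knee surgery by post or telephone at 3 and 6 months. Section 4.8 already lists the two scales as patient-reported.
- State how a stop for harm counts in the composite, and report an analysis of all randomised patients beside the per-protocol one. Without this, editing Section 5.3 would not bring these patients into the comparison.

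The cost is a wording amendment, a few extra mailings or calls, and a small difference in mode of collection for the patients concerned. The sample size is unchanged. The change concerns data collection only and leaves untouched when, or for what reason, treatment is stopped.
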